### Participant timeline {13}

Each patient participates in the study for a period of 9 months. The patient benefit from a consultation with the physician on the day of inclusion at D0 and then during three follow-up visits at 3 (M3), 6 (M6), and 9 (M9) months (Table 1). During each consultation, the outcomes listed above are collected. Randomization is performed by the coach at D0 and if the patient is in the Immediate solution group, he gives the wristband to the patient and performs the first coaching session. For the Delayed solution group, the delivery of the wristband and the first coaching session are performed at 3 months. For both groups, the coach conducted the three other coaching sessions by telephone after 7 days, 1 and 2 months of wristband’s use. A follow-up booklet is given to the patient at D0. The patient must report on it at the end of each week their consumption of drug and complementary treatments. One week per month, the patient indicates each day the pain score on a VAS. At the end of each month, he indicates the activity carried out during the month as well as the medical and paramedical consultations he has received.

**Table 1 Tab1:** Study schedule of enrolment, follow-up, and assessments

Name of the visit	Eligibility screen	Enrolment	Follow-up			Phone calls							
Temporality	D0–3W	D0	M3	M6	M9	D7	M1	M2	M3+7D	M4	M5	M7	M8
Time window for the visit	± 2W		[− 1W/+ 2W]			±2D	± 1W		±2D	± 1W			
Location of the visit	By phone	Pain center											
Information	✓	✓											
Informed consent		✓											
Clinical examination^a^		✓	✓	✓	✓								
Urine HCG if necessary		✓											
Questionnaires^b^		✓	✓	✓	✓								
Randomization		✓											
Collection of adverse events			✓	✓	✓	✓I	✓I	✓I	✓D	✓D	✓D	✓ID	✓ID
Personalized coaching^c^		✓I	✓D			✓I	✓I	✓I	✓D	✓D	✓D		
Reminder to complete the follow-up booklet							✓D	✓D		✓I	✓I	✓ ID	✓ ID

*M* month, *W* week, *D* day

^a^Clinical examination: height, weight, PAS, PAD, and pain on VAS

^b^Questionnaires: FIQ/PSQI/HAD/IMF20/EQ 5D-5L/GPAC/PGIC and CGIC (not at D0)

^c^Personalized coaching: in each box, it is specified for which group(s) it is realized. *I* Immediate solution, *D* Delayed solution

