### Outcomes {12}

The primary outcome is to compare between the two randomization groups the percentage of patients who significantly improve their fibromyalgia-specific quality of life between the inclusion visit at D0 and the 3-month visit (M3). The fibromyalgia-specific quality of life is evaluated with the French-validated version of the self-questionnaire Fibromyalgia Impact Questionnaire (FIQ). A decrease in FIQ score of 14% or more is considered clinically meaningful [29].

In secondary outcomes number 1 to 5, we compared between the two groups the evolution from D0 to M3 of criteria related to the symptoms of fibromyalgia patients:Questionnaires: Quality of sleep on the Pittsburg Sleep Quality Index (PSQI); Anxiety and depression on the Hospital and Anxiety Depression scale (HAD); Fatigue on the Multidimensional Fatigue Inventory questionnaire (MFI 20); General quality of life on the EQ-5D-5L; Physical activity on the Global Physical Activity Questionnaire (GPAC)Average pain score over the week on a visual analogic scale (VAS)Class, dose, and the number of analgesic, antidepressant, and sleeping pill intake. Patient-reported dose and number of these treatments in his home follow-up bookletConsumption of care in relation to the symptoms of fibromyalgia reported each week by the patient in his home follow-up booklet: care (procedures, medical consultations, hospitalizations); complementary care (acupuncture, osteopath, naturopath, etc.); psycho-behavioral therapies; complementary treatments (phytotherapy, homeopathy, food supplements)Number of steps measured by the subject’s smartphone and collected through the Fibrepik mobile application.

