In secondary outcomes 6 to 9, we evaluated:6.Impression of the disease change at M3 by the patient on the Patient Global Impression of Change (PGIC) scale and by the caregiver on the Clinician Global Impression of Change (CGIC) scale7.Solution and wristband objectives: Frequency of use of the wristband on the 6-month period of use it. The frequency of use is an extract of the wristband log file; Usability of the wristband on the modular evaluation of key Components of User Experience (meCUE) questionnaire at M6 for patients of the Immediate solution group and at M9 for patients of the Delayed solution group; Solution satisfaction questionnaire (questionnaire created by the sponsor) at M6 for patients of Immediate solution group and at M9 for patients of Delayed solution group8.Number, description, and classification (serious/non-serious) of adverse effects9.Primary outcome and secondary outcomes 1 to 6 evaluated at 6 and 9 months.

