## Statistical methods

### Statistical methods for primary and secondary outcomes {20a}

Descriptive analyses will be expressed by means − standard deviations and medians − interquartiles for quantitative data, as well as numbers and percentages for qualitative data.

The analysis of the primary endpoint will be performed using a Fisher exact test. For secondary endpoints at M3, all endpoints evaluating a change in score between D0 and M3 will be analyzed via bivariate linear regressions, considering the randomization group and the value of the score at D0. Qualitative criteria will be analyzed using a Fisher test. The secondary endpoint 8 is descriptive and will follow indications for descriptive analysis. For secondary endpoint 9, since analysis considers several measurement points with different states, mixed regressions (linear or logistic depending on the type of variable) will be implemented. Data at M6 from the delayed intervention group will be analyzed for comparison at M3 via a McNemars test (test of proportions for paired data).

These analyses are planned in two stages: (i) all criteria evaluated at 3 months will be performed when all patients have made their follow-up visit at M3 and (ii) all criteria evaluated at 6 and 9 months will be analyzed when the follow-ups at M9 of all patients are completed.

The results will be presented in accordance with the recommendations of the CONSORT Statement. These analyses will be implemented after a consistency check and a freeze of the database, in accordance with the good practices of the Grenoble Alps University Hospital. The software used will be Stata 15 or a more recent version (StataCorp LLC).

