### Methods in analysis to handle protocol non-adherence and any statistical methods to handle missing data {20c}

All analyses will be performed in Intention-To-Treat. In addition to this analysis, a per-protocol analysis will be performed by keeping only patients who have been compliant with the treatment. We consider that a patient is compliant if during the first 3 months of solution use, we observe at least 80% of days with two or more sessions per day. This number of sessions is an extract of the wristband log file.

Missing data within the FIQ questionnaire will be accounted for following the recommendations of the scale authors [38]. A sensitivity analysis of the primary endpoint will be performed by imputing missing data not managed via the FIQ use recommendations via multiple imputation if these missing data represent between 5 and 20% of the total data.

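### Pain is recorded for one week in every month, but the stated M3 analysis uses a single time point, so the month 1 and 2 pain weeks of the randomised comparison enter no stated analysis

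*Protocol article*

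**What the plan says.** **Collection.** Under Participant timeline {13}: "One week per month, the patient indicates each day the pain score on a VAS". The booklet is handed over at D0. Table 1, footnote a, also places a pain VAS in the clinical examination at D0, M3, M6 and M9.

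**Endpoint.** Outcomes {12} lists secondary outcome 2 as "Average pain score over the week on a visual analogic scale (VAS)". For outcomes 1 to 5 it says "we compared between the two groups the evolution from D0 to M3 of criteria related to the symptoms of fibromyalgia patients". Outcome 9 is "Primary outcome and secondary outcomes 1 to 6 evaluated at 6 and 9 months".

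**Analysis.** Statistical methods {20a}: "all endpoints evaluating a change in score between D0 and M3 will be analyzed via bivariate linear regressions, considering the randomization group" and the score at D0. Mixed models appear only later: "For secondary endpoint 9, since analysis considers several measurement points with different states, mixed regressions".

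**Missing data.** The only imputation named in section {20c} is for the FIQ: "A sensitivity analysis of the primary endpoint will be performed by imputing missing data not managed via the FIQ use recommendations". The same section declares intention-to-treat for all analyses but does not say how a missing pain score is handled.

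**The concern.** D0 to M3 is the only period in which the solution is compared with standard care alone, and the article's rationale treats pain as a central symptom. In that period the booklet should yield three weekly means per patient. The stated model uses one post-baseline value, and the endpoint 9 mixed models concern M6 and M9 and are run in the second analysis stage.

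Two things are at stake. The first is precision: months 1 and 2 carry information about month 3 that is not used. The second is the missing-data assumption. A regression on group and D0 value is unbiased only if missingness of the M3 value is unrelated to M3 pain once group and D0 pain are known. If patients in one arm stop the booklet after a painful second month, that fails, and the arm that loses its high-pain patients looks better than it is.

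Some difference between arms is conceivable from the schedule. Patients know their group. At M1 and M2, Table 1 gives the Delayed group a booklet-reminder call and the Immediate group a coaching call, although app reminders go to both.

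**Working it through.** **Plan's own figure.** None is given for pain. The sample size is for FIQ response, 50% versus 25%, and it reproduces: [1.960·√(2·0.375·0.625) + 1.282·√(0.25 + 0.1875)]² / 0.25² = (1.342 + 0.848)² / 0.0625 ≈ 76.7, so 77 per group. With 10% added, 77 × 1.10 ≈ 85. Nothing below changes it. The 85 per group is used as the number randomised.

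**Which time points are analysed at M3?**

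| Pain data before or at M3 | Stated M3 analysis |
|---|---|
| Diary weeks, months 1 and 2 | none |
| Diary week, month 3 | only if it is the source of the M3 value |
| Clinic VAS at M3 | only if it is the source of the M3 value |

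Months 1 and 2 are unused on either reading.

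**Assumed inputs** (the document gives none): SD 2 points; correlation of D0 with each month 0.5; adjacent months a = 0.6 to 0.8; months 1 and 3 correlated at a²; month-3 week missing in 10 to 30%. Only the 10% has an anchor, the loss-to-follow-up allowance in Sample size {14}. Months 1 and 2 are taken as observed.

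**Precision, random missingness.** Let R² be the share of month-3 variance explained by months 1 and 2 after adjusting for D0. With a fraction m missing, Var(mixed) / Var(planned) = 1 − m·R², so the planned estimate has excess variance 1/(1 − m·R²) − 1.

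- a = 0.6: the correlations given D0 are (0.6 − 0.25)/0.75 = 0.467 for adjacent months and (0.36 − 0.25)/0.75 = 0.147 for months 1 and 3. R² = (0.147² + 0.467² − 2·0.147·0.467²)/(1 − 0.467²) = 0.224.
- a = 0.8: 0.733 and 0.520 in the same way, so R² = 0.538.

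| Missing | a = 0.6 | a = 0.8 |
|---|---|---|
| 10% | 1/(1 − 0.0224) − 1 = 2% | 1/(1 − 0.0538) − 1 = 6% |
| 30% | 1/(1 − 0.0673) − 1 = 7% | 1/(1 − 0.1615) − 1 = 19% |

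If instead all pairs, D0 included, share one correlation of 0.5 to 0.8, R² is 0.167 to 0.274. The variance reduction m·R² is then about 2 to 3% at 10% missing and 5 to 8% at 30%.

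**Bias, month-3 dropout related to pain in one arm** (same missing rate, at random, in the other arm; by simulation):

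| Dropout depends on | Missing | Planned regression | Using months 1 and 2 |
|---|---|---|---|
| Month-2 pain, log-odds 1 per SD | 10% | 0.07–0.10 | at most 0.01 |
| Month-2 pain, log-odds 1 per SD | 30% | 0.18–0.29 | at most 0.01 |
| Month-2 pain, weaker | 10% | 0.02–0.04 | at most 0.01 |
| Unrecorded month-3 pain, log-odds 1 per SD | 10% | 0.13–0.14 | 0.07–0.10 |
| Unrecorded month-3 pain, log-odds 1 per SD | 30% | 0.38–0.39 | 0.15–0.30 |

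**Scale.** The planned standard error is √(2·4·0.75/(85·(1 − m))): √(6/76.5) = 0.28 at 10% missing and √(6/59.5) = 0.32 at 30%. The strong month-2 mechanism therefore gives a bias of 0.07/0.28 to 0.10/0.28, about 0.25 to 0.36 standard errors, at 10% missing, and 0.18/0.32 to 0.29/0.32, about 0.6 to 0.9, at 30%.

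**The case against.** The strongest objection is that the M3 source is not stated. The clinic VAS is scheduled at exactly the time points of outcomes 2 and 9, and it is the only D0 pain value the article describes, since the booklet is first handed over at D0. A reader might infer that every patient without a month-3 diary week is dropped. The document does not say so, and if the clinic VAS is the source, a missed diary week removes nobody. The wording of outcome 2, an average over a week, favours the diary without settling it. This stands, and it limits the drop-out point to one of the two readings.

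A reader might also infer that secondary outcomes will be analysed on complete cases because imputation is named only for the FIQ. That is silence in a condensed article, and such detail may sit in the full protocol or analysis plan. It is no finding here. What remains is a stated model choice: section {20a} fixes the M3 regression for all score changes and names mixed regressions only for endpoint 9.

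Third, baseline-adjusted regression at a pre-stated time point is a standard, valid analysis, and nothing in the documents shows that dropout will follow month-2 pain in one arm. The article expects very few losses, sends reminders to both groups and has eCRF checks for missing data. This also stands. It is why the gain is called modest. The expectation of few losses is argued from consultations and the FIQ, however, and diary weeks may be missed more often than visits.

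**Conclusion.** The point holds as an improvement to a stated choice, not as an error that invalidates the analysis. No stated analysis uses the month 1 and 2 pain weeks, whichever source supplies the M3 value. A mixed model on months 1 to 3 relaxes the missing-data assumption to dependence on recorded month 1 and 2 pain.

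Under the assumed SD and correlations, at the document's only loss figure of 10%, this avoids at most about a third of a standard error of bias. The larger figures need 30% missing, for which the document gives no support. The model reduces bias but does not remove it if dropout depends on unrecorded month-3 pain. With complete diaries the gain at M3 largely vanishes.

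A reader might take this as casting doubt on the trial's main result. It does not: the FIQ comparison and its sample size are untouched, and pain is an unpowered secondary outcome.

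**What to change.** State that the diary weekly mean is the pain endpoint, and name the source of the D0 value; the clinic VAS is the only one described. Analyse the weekly means of months 1, 2 and 3 in a linear mixed model with arm, month, arm-by-month, the D0 VAS and D0-by-month, preferably leaving the covariance of the three months unstructured. Report the M3 between-arm difference as the estimate, so the target does not change. An average over months 1 to 3 would be a different estimand and is not proposed.

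The cost is a change of analysis wording and a little more analysis work. The data are already collected and the plan already uses mixed regressions elsewhere. Extending the same model to months 4 to 9 for outcome 9 is optional; no calculation here supports it.

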#### Immediate solution description

The “Immediate solution” group consists of (i) from D0 to M3—3 months with the solution (wristband, Fibrepik App, and coaching) in addition to the standard of care, (ii) from M3 to M6—3 months with the wristband and Fibrepik App in addition to the standard of care, and (iii) from M6 to M9—3 months with the standard of care. These 3 last months with the standard of care is to evaluate the reminiscence effects of the millimeter waves.

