### Strategies to improve adherence to interventions {11c}

The coach has access for each patient to the data of the Fibrepik application: the wristband usage data and step counts. If necessary, during the first 3 months of the wristband use, the coach can send a notification to the patient’s smartphone to remind them, for example, to perform sessions or to reinforce the planned coaching sessions scheduled at 7 days (D7) and then after one and 2 months of starting to use the solution. Sending a notification is also used to remind patients in both groups to complete their home follow-up booklet.

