### Adverse event reporting and harms {22}

This clinical study is considered by the French law like a low or negligible risk study. So, the vigilance of the clinical trial is identical to that of medical care. However, any adverse event is collected immediately in the eCRF and the sponsor is informed by an email alert from the eCRF. If it is an adverse effect, an analysis of the internal data of the wristband is performed to best describe this event. In case of serious adverse effects, a declaration to the health authority would be made by the sponsor.

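### Between D7 and M5, Table 1 schedules adverse-event enquiry only for the group being coached, so prompts are 4:1 (Immediate:Delayed) in D0–M3 and 1:4 in M3–M6

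*Protocol article*

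**What the plan says.** Table 1 of the protocol article (Participant timeline {13}) has three rows that matter here.

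- "Collection of adverse events": both groups at M3, M6 and M9 and at the M7 and M8 calls; Immediate only at D7, M1 and M2; Delayed only at M3+7D, M4 and M5.
- "Personalized coaching": Immediate at D0, D7, M1 and M2; Delayed at M3, M3+7D, M4 and M5; nobody after M5.
- "Reminder to complete the follow-up booklet": Delayed at M1 and M2; Immediate at M4 and M5; both groups at M7 and M8. All of these stand under the phone-call columns.

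The section on the Immediate solution describes its second phase as "from M3 to M6—3 months with the wristband and Fibrepik App in addition to the standard of care" and its third as "from M6 to M9—3 months with the standard of care". The Delayed group has its own wristband-without-coaching phase from M6 to M9.

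Secondary outcome 8 in Outcomes {12} is "Number, description, and classification (serious/non-serious) of adverse effects", and the statistical methods section {20a} makes it descriptive. The harms section {22} adds that "any adverse event is collected immediately in the eCRF", with an e-mail alert to the sponsor.

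**The concern.** How many adverse events are recorded depends partly on how often patients are asked. If one arm is asked four times and the other once, a difference in counts mixes any effect of the solution with a difference in enquiry. D0–M3 is the only period in which the randomised groups differ as solution versus standard care, so it is the only one that can supply a concurrent background rate. Fibromyalgia brings many somatic complaints, and such a rate helps to separate adverse effects of the device from events that would have happened anyway.

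A second issue lies within the device-use period. The schedule drops the Immediate group's monthly enquiry when coaching ends, although the wristband stays in use, and restores it once the wristband is withdrawn. The wristband-alone phase is therefore observed differently in the two groups, and pooling device-use time across them would combine unlike ascertainment.

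**Working it through.** The plan states no count of adverse-event contacts, so there is no figure to reproduce. The counts below come directly from the Table 1 ticks.

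**Scheduled enquiries by period**

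| Period | Immediate | Delayed | I:D |
|---|---|---|---|
| D0–M3 | D7, M1, M2, M3 = 4 | M3 = 1 | 4:1 |
| M3–M6 | M6 = 1 | M3+7D, M4, M5, M6 = 4 | 1:4 |
| M6–M9 | M7, M8, M9 = 3 | M7, M8, M9 = 3 | 3:3 |
| Total | 4 + 1 + 3 = 8 | 1 + 4 + 3 = 8 | 8:8 |

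**By phase of device use** (six months of wristband per group)

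- Whole wristband period: Immediate D7, M1, M2, M3, M6 = 5; Delayed M3+7D, M4, M5, M6, M7, M8, M9 = 7.
- Wristband without coaching: Immediate M6 = 1; Delayed M7, M8, M9 = 3.
- Off the wristband: Immediate M7, M8, M9 = 3; Delayed M3 = 1.

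**Contacts that carry a reminder but no enquiry**

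Comparing the reminder row with the adverse-event row gives four cells: Delayed at M1 and M2, Immediate at M4 and M5. At M7 and M8 the same kind of contact carries both items, for both groups and with no coaching. The plan thus already combines them, and the article gives no reason for not doing so earlier.

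**With those four cells ticked**

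- D0–M3: 4 against 1 + 2 = 3, so 4:3.
- M3–M6: 1 + 2 = 3 against 4, so 3:4.
- Total: 8 + 2 = 10 in each group.
- Whole wristband period: 5 + 2 = 7 against 7. Wristband without coaching: 1 + 2 = 3 against 3. Off the wristband: 3 against 1 + 2 = 3.

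The remaining difference within calendar periods is the early call one week after device delivery (D7 for Immediate, M3+7D for Delayed). By phase of device use the counts become equal.

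**The case against.** **Events can be reported at any time.** The harms section has every adverse event entered immediately. This stands to the extent that 4:1 counts scheduled prompts and not total ascertainment. But immediate entry applies once staff know of an event; it schedules no question. The home booklet, as the article describes it, records treatments, pain, activity and consultations, not adverse events.

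**The outcome is descriptive, and controls cannot have device effects before M3.** Both are true. No between-group safety test is planned, and outcome 8 concerns adverse effects. This limits the consequence but does not remove it: Table 1 and the harms section collect adverse events in both arms, and descriptive counts also depend on how often patients were asked.

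**Closer contact just after device delivery is reasonable, and the study is classed as low or negligible risk.** That can justify D7 and M3+7D. It does not explain why Immediate patients are asked at M7 and M8 off the wristband but not at M4 and M5 while using it.

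**The reminder may not be a spoken call.** Strategies to improve adherence {11c} says "Sending a notification is also used to remind patients in both groups to complete their home follow-up booklet". Table 1 puts the reminder under phone calls, but a conversation is not certain. This affects the cost of the remedy, not the counts.

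**Stronger readings to avoid.** A reader might infer that adverse events are collected only while a group is being coached. Table 1 contradicts this: both groups are asked at M6, M7, M8 and M9, when nobody is coached, and at M3. A reader might also take 4:1 to describe the whole trial, but it holds for D0–M3 only. Nor are events in Immediate patients between M3 and M6 never asked about: they are covered at M6, by recall over three months.

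**Conclusion.** The point holds in a limited form. From D7 to M5, scheduled adverse-event enquiry follows coaching. That gives 4:1 in the randomised comparison period, 1:4 in the next three months, and one check against three in the wristband-alone phase. The counts rest only on the Table 1 ticks, read as they stand.

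The effect is on the interpretation of secondary outcome 8 and of any adverse-event table by group or by phase of device use. The primary endpoint is not affected.

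The size of any resulting bias cannot be taken from the documents, because they give no capture rate per enquiry. Purely as an assumption, if a single three-month recall captured 50% to 80% of events and monthly asking 90%, equal true rates would appear as a ratio between 0.9/0.8 = 1.1 and 0.9/0.5 = 1.8. That range follows from the assumed rates and leaves out spontaneous reports. It shows direction only and should not be quoted as an estimate.

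**What to change.** **Schedule.** In Table 1, tick adverse-event collection for Delayed at M1 and M2 and for Immediate at M4 and M5, using the same scripted open question in every group and at every contact, as part of the reminder contacts already listed, as at M7 and M8. This gives 4:3 and 3:4, not equality; D7 and M3+7D stay one-sided, and the protocol should say so. The cost is a few minutes per contact and a small eCRF change. If the reminder goes out only as an app notification, a prompted reply or a short call would be needed. That is not free, since Recruitment {15} names coach availability as the main constraint.

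**Reporting.** Inclusions ended on April 1, 2022 (Trial status), so the last M5 contact fell around September 1, 2022, and the article appeared on September 5. For this trial the schedule change probably comes too late, and the reporting part matters more:

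- present adverse events by period and by on- or off-device status, with person-time;
- show the contact at which each event was reported, or that it was spontaneous;
- state the unequal enquiry schedule beside the table;
- do not treat counts restricted to the visits common to both groups as unbiased. Events that Immediate patients reported at D7, M1 or M2 may not be recorded again at M3, so such a restriction could undercount that group.

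This needs no new data beyond the date and source of each report.
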